## Abstract

*Introduction*: Water accounts for about 75% of brain mass. Cognitive performances and mood may be impaired by hypohydration and improved by water supplementation. Two surveys conducted in China demonstrated that a large proportion of adults and children drank less fluid than the amounts recommended by the Chinese Nutrition Society. The association between hypohydration and cognitive performance has not been reported in China. The purpose of this study is to explore the effect of water supplementation on cognitive performances and mood among male college students in Cangzhou, China. *Methods and Analysis*: A randomized controlled trial is designed to test the hypothesis. A total of 68 male college students aged 18–25 years will be recruited and randomly assigned into water-supplementation group (WS group, *n* = 34) and no water-supplementation group (NW group, *n* = 34) after an overnight fasting, i.e., without eating foods and drinking fluid for 12 h. The first morning urine will be collected to determine urine osmolality on the water supplementation day. Cognitive performances and mood will be performed before water supplementation by researchers with questionnaire. Subjects in the WS group will drink 400 mL purified water within 5 min, while those in NW group will not drink any fluid. One hour later, urine will be collected and urine osmolality, cognitive performances and mood will be measured again. Mixed model of repeated measures ANOVA will be used to investigate the effect of water supplementation on cognitive performances. The study would provide information about the benefit of water supplementation on cognitive performances. *Ethics and Dissemination*: The study protocol is reviewed and approved by the Ethical Review Committee of the Chinese Nutrition Society. Ethical approval project identification code is CNS-2015-001. Results will be published according to the CONSORT statement and will be reported in peer-reviewed journals. *Trial registration*: Chinese clinical trial registry. Identifier: ChiCTR-IOR-15007020. Registry name “The effect of hydration on cognitive performance”.

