### 2.3. Sample Size Calculation

The variable used for the calculation of sample size is digit span. Digit span is used to assess short-term memory. It was reported that the average values of digit span for subjects with water supplementation and without water supplementation were 10.5 and 11.5, respectively [18]. The values was taken as reference for our study and 80% power is set. SAS 9.2 (SAS Institute Inc., Cary, NC, USA) is used to calculate the sample size. Only male students will be studied, for the reason that women’s menstrual cycle may have impacts on urine indicators and cognitive performances. In addition, 10% drop-out rate is taken into account. Eventually, a total of 68 subjects will be needed. 

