#### 2.6.5. Groups of Subjects

On day 9 (the water supplementation day), all subjects will be asked to arrive at the designated place at 8:00 AM. After being encoded according to student ID, subjects will be randomly assigned to the water-supplementation group (WS group, 34) and no water-supplementation group (NW group, 34) using random number table to generate random sequence. Baseline height, weight, waist circumferences, blood pressure and blood glucose will be measured (test 1: before water supplementation) following the standardized procedures. The first morning urine samples will also be collected and tested. At 8:30 AM, cognitive performances, mood and subjective sensation of satiety, hunger, sleepiness and thirst will be tested (test 1).

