#### 2.6.6. Water Supplementation

At 9:00 AM, subjects in the WS group will drink 400 mL purified water within 5 min with uniform cups in one designated place, while those in NW group will not drink any water or beverages in another designated place. Subjects in NW group will not be told the intervention of WS group. During the interval before the next test, all subjects will be asked to sit at their own seat without physical activity. They will be asked not to eat foods, drink water/beverages, and urinate. One hour after water supplementation (at 10:05 AM), blood pressure and blood glucose will be measured again in designated place (test 2: after water supplementation). Urine samples will be collected, stored and tested again (test 2). At 10:25 AM, cognitive performances, mood and subjective sensation of satiety, hunger, sleepiness and thirst will be measured again (test 2). Temperature and humidity will be recorded at 8:00 AM. During the period of the study, subjects can quit at any time for side effects, such as syncope. The study procedure is shown in Figure 2.

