### 2.19. Data Collection, Entry and Statistical Analysis

Data collection: Researchers will be trained about the trial process, the use of questionnaires and laboratory tests. Subjects will be trained to be familiar with the related questionnaire and the requirements in the study. Some indicators are measured twice to ensure their accuracy, such as height, weight, waist circumstance and blood pressure. If subject withdraw the trial, his data will not be analyzed. All the questionnaires will be stored for regularly checked and rechecked by data monitoring committee. 

*Data entry*: All data will be recorded and entered into Epi Data 3.1 twice to ensure the accuracy by trained researchers. 

*Statistical analysis*: SAS 9.2 (SAS Institute Inc., Cary, NC, USA) will be used for statistical analyses. Quantitative parameters for subjects will be presented as mean ± standard deviation; binary classification data (hypohydration) will be presented as n ± percentage. Quantitative parameters at test 1 between two groups will be compared with the method of Student’s *t*-test (for normally distribution) and Mann-Whitney *u*-test (for abnormally distribution); binary classification data (hypohydration) at test 1 between two groups will be compared with the method of Chi-square test. Mixed model of repeated measures (ANOVA) will be used to investigate the effect of water supplementation on changes in urine index, mood and cognitive performances, whilst covarying age, BMI, hunger, satiety, sleepiness, blood pressure, blood glucose, body area and fluid intake. Significance levels will be set at 0.05 (*p* < 0.05, 2-tailed) with 95% confidence intervals (95% CI). Data of subjects without compliance will be included in data analysis.

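### The analysis of change omits each outcome's own test 1 value as a covariate; adjusting test 2 for test 1 would be more precise at no extra data cost

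*Protocol article*

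**What the plan says.** Section 2.19 labels its repeated-measures mixed model an ANOVA and says that it "will be used to investigate the effect of water supplementation on changes in urine index, mood and cognitive performances". Nine covariates are then listed in the same sentence: "whilst covarying age, BMI, hunger, satiety, sleepiness, blood pressure, blood glucose, body area and fluid intake". The Abstract names the same model: "Mixed model of repeated measures ANOVA will be used to investigate the effect of water supplementation on cognitive performances". The Discussion repeats the nine covariates and presents them as a strength. Neither list contains the test 1 value of the outcome being analysed.

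That value exists for cognition and mood in every subject tested. Section 2.6.5 places it before the water: "At 8:30 AM, cognitive performances, mood and subjective sensation of satiety, hunger, sleepiness and thirst will be tested (test 1". Section 2.6.6 places the repeat after it: "At 10:25 AM, cognitive performances, mood and subjective sensation of satiety, hunger, sleepiness and thirst will be measured again (test 2". Apart from being one end of the change, test 1 values appear in section 2.19 only in a between-group baseline comparison, by t-test or rank test: "Quantitative parameters at test 1 between two groups will be compared with the method of Student’s".

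On size, section 2.3 says "The variable used for the calculation of sample size is digit span" and takes reference group means that "were 10.5 and 11.5, respectively". With 80% power and 10% drop-out it arrives at 68 subjects. It states no SD and no correlation between the two tests, and does not say whether the calculation was for test 2 values or for change.

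**The concern.** A subject's own score before the intervention is usually the best single predictor of his score afterwards. A change score uses it with a fixed coefficient of 1; adjustment uses it with the coefficient that the data support. When the correlation is below 1, the fixed coefficient over-corrects. This adds noise, and it carries regression to the mean into the estimate whenever the groups happen to differ at test 1.

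The other covariates do not obviously make up for this. Characteristics fixed within a person, such as age, BMI and body surface area, cancel out of a within-person contrast when entered as main effects. In a trial of 68 subjects, the stake is a wider confidence interval than the collected data allow, and an estimate that moves more with chance imbalance.

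**Working it through.** **Inputs from the article.** Difference in digit span 1.0 (absolute difference of the two reference means, section 2.3); power 80%; drop-out 10%; 34 per group; two-sided 0.05 (section 2.19). After 10% drop-out, 34 × 0.9 = 30.6, so about 31 per group are analysed.

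**Assumptions, not in the article.** The SD; the test 1–test 2 correlation ρ; equal SD at both tests.

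**The plan's own figure.** Without an SD, 68 cannot be reproduced forward. Solving backwards for a plain two-group comparison:

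- n per group = 2 × (1.96 + 0.84)² × SD² / 1² ≈ 15.7 × SD².
- SD 1.38: 15.7 × 1.904 = 29.9, so 30 per group; 30 / 0.9 = 33.3, so 34 per group, total 68.
- By the same formula, SD 1.0 gives 36 in total, SD 1.5 gives 80 and SD 2.0 gives 140.

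So 68 fits an SD of about 1.35 to 1.38, if the sizing was of this kind. With 31 analysed per group, the SD giving exactly 80% power is 1.38 by the t distribution and 1.41 by the normal approximation.

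**Variance per subject.**

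- Change (group by time with two tests): 2(1 − ρ) × SD².
- Test 2 adjusted for test 1: (1 − ρ²) × SD².
- Ratio, adjusted to change: (1 − ρ²) / [2(1 − ρ)] = (1 + ρ)/2. This is below 1 for every ρ below 1 and does not depend on the SD.

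**Power.** Noncentral t, 31 per group, difference 1.0, SD 1.38:

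| ρ (assumed) | Variance, change (× SD²) | Variance, adjusted (× SD²) | Reduction | Power, change | Power, adjusted |
|---|---|---|---|---|---|
| 0.3 | 1.40 | 0.91 | 35% | 66% | 84% |
| 0.5 | 1.00 | 0.75 | 25% | 80% | 90% |
| 0.7 | 0.60 | 0.51 | 15% | 95% | 98% |

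A simulation of 4,000 trials per correlation agrees: 67% against 83%, 80% against 90%, and 96% against 97%.

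**Chance imbalance.** One standard error of the test 1 group difference is 1.38 × √(2/31) = 0.35 points. A test 1 difference of that size shifts the change estimate by (1 − ρ) × 0.35, about 0.18 points at ρ = 0.5, against a target of 1 point. Adjustment removes that shift.

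**The case against.** The strongest reply is that the planned analysis is sound. Under randomisation the group-by-time test is unbiased with the correct type I error, and test 1 is not ignored, since it is one of the two responses. The point is therefore one of efficiency between two valid methods. That stands. At high correlation the gain is also small: 95% against 98% power at 0.7.

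A reader might infer that the trial is underpowered. The article does not support this. The SD of 1.38 is back-solved on the assumption that 68 was sized on test 2 values, and under that assumption the planned analysis falls below 80% only if the correlation is under 0.5. The same tests are repeated on the same morning, less than two hours apart, and nothing in the article suggests so low a correlation. If the sizing SD was that of the change, the planned analysis has its 80% by construction.

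A reader might also fear that the group main effect, which averages scores before and after the water, would be read as the treatment effect. Section 2.19 speaks of an effect on changes, which points to group by time. Naming the model term is detail that a separate analysis plan may hold.

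Two caveats on the model also stand. A mixed model with a common test 1 mean in both groups would be about as efficient as ANCOVA; the article states no such constraint, but its wording does not rule it out. Hunger, satiety, sleepiness, blood pressure and blood glucose are measured at both tests. If they enter as time-varying covariates, the planned test is no longer exactly a t-test on change and the formulas above are approximate.

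The objection does not remove the core. The article itself states the model, the target and the covariates, and the baseline value of the outcome is not among those covariates.

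**Conclusion.** The point holds as a matter of precision, not of validity. As written, the analysis gives up about 35%, 25% or 15% of the variance at assumed correlations of 0.3, 0.5 or 0.7, and leaves the estimate more sensitive to chance differences at test 1. The direction of the loss is algebraic, given equal SDs at the two tests. Its size depends on a correlation that the article does not give, and the power figures depend also on the back-solved SD. A shortfall against 80% is possible under those assumptions but is not shown. The change is worth making because the data are already collected.

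**What to change.** Add to section 2.19 a sentence such as: the treatment effect for each quantitative outcome is the WS–NW difference at test 2, adjusted for the test 1 value of the same outcome, estimated by ANCOVA or by a mixed model with a common test 1 mean across groups, and reported with its 95% CI. It would help to state in section 2.3 the SD behind the 68, whether it refers to test 2 values or to change, and any correlation assumed.

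The cost is a sentence or two. No new data are needed, and the SAS software already planned can fit either model. The change does not by itself bring back subjects without test 2: section 2.19 separately excludes the data of those who withdraw, and that rule would remain.

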### 2.2. Study Design and Assignment of Interventions

This is a randomized controlled trial. After being encoded according to student ID, recruited subjects will be randomly assigned to the water-supplementation group (WS group, 34) and no water-supplementation group (NW group, 34) using random number table to generate random sequence by investigators. Measurements on blood pressure, blood glucose, urine osmolality, urine sodium concentration, urine specific gravity, test of subjective sensation of satiety, hunger, sleepiness and thirst, mood and cognitive performances will be performed before and after water supplementation (Figure 1). All items from the World Health Organization Trial Registration Data Set are shown in Table 1.

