The present study design has both strengths and weaknesses. In terms of strength, first, the possible confounding factors are considered relatively comprehensive. Age, BMI, hunger, satiety, sleepiness, blood pressure, blood glucose, body area and fluid intake will be measured and included as covariates to make a more accurate conclusion. Second, a randomized controlled design will be used to reduce bias. Third, hypohydration state will be induced by the simple method of fluid restriction, which are meaningful to explain its effect on cognitive performance more clearly. Fourth, subjects will be fasted for 12 h in order to eliminate the influence of dietary on the test. In most previous studies, the group without water supplementation was subjectively considered as hypohydration group, which may be not consistent with the actual hydration state. In our study, urine osmolality will be measured in order to objectively evaluate the changes of hydration state. In terms of weakness, gender differences will not be explored in our study. In addition, the effect of long-term water supplementation on cognitive performance will not be studied. The mechanism will also not be explored.

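### The nine covariates fixed for the model of change do not support the accuracy claimed for them: as fixed-value main effects they cancel from the water effect, and as covariate-by-time terms they may cost up to 7-8 power points

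*Protocol article*

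**What the plan says.** Section 2.19 specifies a mixed repeated-measures model for changes in urine index, mood and cognition, "whilst covarying age, BMI, hunger, satiety, sleepiness, blood pressure, blood glucose, body area and fluid intake". The test is two-sided ("Significance levels will be set at 0.05"). The same section leaves men who withdraw out of the analysis.

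Section 3 (Discussion) names this covariate set as the first strength of the design. The variables "will be measured and included as covariates to make a more accurate conclusion".

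Section 2.3 sizes the trial on digit span from two group means: "the average values of digit span for subjects with water supplementation and without water supplementation were 10.5 and 11.5, respectively". It adds that "80% power is set" and allows for 10% drop-out, giving 68 men, 34 per group (section 2.2). It states no SD and mentions no covariate adjustment.

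Section 2.9 derives both BMI and body surface area from one measured height and weight. Section 2.8 yields one habitual fluid intake figure per man. By contrast, sections 2.6.5 and 2.6.6 record blood pressure, glucose and the sensation ratings both before and after the water. The article does not say whether covariates enter as main effects or as covariate-by-time terms.

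**The concern.** The claim that the list makes the conclusion more accurate can be tested against the model to which it is attached. With two occasions, the water effect on change is the group-by-time term. A covariate with a single value per man either enters as a main effect, and then cannot touch that term, or interacts with time, and then uses a degree of freedom and adds chance imbalance to the comparison. In the second case it helps only if it predicts change over about an hour.

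At stake is a modest loss of precision in a small trial, together with a published strength that the specified model may not deliver. A simpler and more efficient adjustment, the test 1 value of the outcome itself, is already collected but is not what section 2.19 describes.

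**Working it through.** **Inputs.** Two-sided alpha 0.05 (2.19); power 80%, difference 1.0 digit, drop-out 10%, total 68 (2.3); 34 and 34 (2.2); covariates k = 9 named, or k = 10 if blood pressure enters as two variables (assumption). Analysed: 68 × 0.9 = 61.2, taken as 31 and 30.

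**The plan's own figure.** The total of 68 cannot be reproduced from stated inputs, because no SD is given. It is reached with an assumed SD of about 1.38: n per group = 2 × (1.960 + 0.842)² × 1.38² / 1.0² = 29.9, so 30. Then 30 / 0.9 = 33.3, so 34 per group and 68 in all.

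**Main effects.** For man i at time t (0 or 1), with group g, covariates x and man effect u:

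y = a + b·g + c·t + e·g·t + γ′x + u + error.

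With complete pairs, y at test 2 minus y at test 1 = c + e·g + error difference. Both γ′x and u drop out, so the estimate of e is the difference in mean change with or without x. A mixed model fitted to one simulated data set of 61 men confirmed this: group-by-time estimate 0.2543 (SE 0.416) with no covariates, and 0.2543 (SE 0.416) with ten.

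**Covariate-by-time terms with baseline values.** This is an analysis of covariance of the change. If the covariates explain a share R² of the variance in change, the expected variance of the group effect is multiplied by (1 − R²)(n − 3)/(n − k − 3):

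- k = 9, R² = 0: 58/49 = 1.18
- k = 10, R² = 0: 58/48 = 1.21

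Power uses the noncentral t with n − 2 − k degrees of freedom, averaged over chance imbalance. The standardised effect on change is set at 0.729, which gives exactly 80% without covariates.

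| R² of change | k = 9 | k = 10 |
|---|---|---|
| 0 | 72.9% | 72.0% |
| 0.10 | 77.3% | 76.4% |
| 0.20 | 81.9% | 81.1% |
| 0.30 | 86.6% | 85.9% |

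Break-even R² is 0.16 for nine and 0.18 for ten.

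**How far the 80% anchor matters.** If the effect of 0.729 belongs to a single score, the result for change depends on the test 1–test 2 correlation ρ, which is not given. With score SD σ, change has variance 2σ²(1 − ρ), and the test 2 score adjusted for test 1 has variance σ²(1 − ρ²).

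| ρ | Change, no covariates | Change, 10 covariates, R² = 0 | Test 2 on group + test 1 |
|---|---|---|---|
| 0.3 | 66% | 58% | 83% |
| 0.5 | 80% | 72% | 89% |
| 0.6 | 88% | 81% | 93% |
| 0.7 | 95% | 91% | 97% |

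**The case against.** Prespecifying a covariate list is legitimate, and an article may leave the exact form of entry to the full protocol or analysis plan. That stands: the silence on form is not the point. The point is that the list is fixed and a benefit is claimed for it.

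A reader might infer that the list must either cancel or cost more power than it returns. The document does not support this, for two reasons. First, the cost depends on R². Above about 0.16-0.18 the covariates gain power, and nothing in the article says where R² lies. Second, the two cases are not exhaustive. Blood pressure, glucose and the three sensation ratings are also measured after the water. If entered as time-varying values, they follow neither case and could remove part of the water effect. In an illustrative simulation in which water lowered such a covariate by an assumed 0.8 units, a total effect of 0.82 was estimated at 0.86 without adjustment and 0.54 with it. Whether the trial would do this is not stated.

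A reader might also infer that the trial falls below its 80%. That is not shown either. With no SD and no ρ, absolute power is unknown, and at ρ of 0.6 or more it stays above 80% even with ten useless covariates.

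It is also fair that the main-effects case does no harm: estimate and standard error are unchanged. What fails there is the claimed gain.

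Finally, redundancy is a minor matter. BMI and body area correlate at about 0.69-0.72 under assumed height and weight distributions, but collinearity among covariates costs the randomised contrast no more than the degrees of freedom used. The article gives no correlation between hunger and satiety.

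**Conclusion.** The point holds in a limited form. For age, BMI, fluid intake and body area entered as main effects, with complete pairs on two occasions, the gain in accuracy is nil. This is exact algebra and needs no assumed figure. For baseline covariates acting on the change, the list may cost 7-8 power points against an unadjusted analysis anchored at 80% (80% to 72.9% or 72.0%), and returns that cost only if R² exceeds about 0.16-0.18. That figure rests on 61 analysed men, on nine or ten single-coefficient terms, and on the 80% anchor. It is an upper figure for useless covariates, not a prediction.

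The document does not establish that the covariates are useless or that power is inadequate. It does leave the accuracy claim in the Discussion unsupported, while a better model is available from data already collected. At ρ = 0.5 the model with only the test 1 outcome gives 89%, against 80% for unadjusted change, and it was ahead at every correlation tried. This is a worthwhile, low-cost improvement and not a threat to validity.

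**What to change.** In section 2.19, make the confirmatory model for each outcome the test 2 value on group plus the test 1 value of the same outcome. Move the wider list to a labelled sensitivity analysis that uses test 1 values for whatever is measured twice and one body-size measure in place of BMI and body area together. In section 3, replace the statement that the covariates make the conclusion more accurate with one saying that the wider adjustment checks robustness.

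The cost is wording only; no new data are needed. The downside is that the primary analysis gives up adjustment for a covariate that might prove prognostic, and the sensitivity model keeps it.

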**Figure 2 ijerph-14-00966-f002:**
[figure not shown]
The study procedure. Note: H (Height); W (Weight); WC (Waist circumference); BP (Blood pressure); BG (Blood glucose); CP (Cognitive performances); POMS (Profile of Mood States); VAS (Visual Analogue Scales).

**Table 1 ijerph-14-00966-t001:** All items from the World Health Organization Trial Registration Data Set (SPIRIT checklist, item 2b).

Data Category	Information
Registration number	ChiCTR-IOR-15007020, Chinese clinical trial registry
Registration State	1008001 Prospective registration
Public title	The effect of hydration on cognitive performance
Scientific title	The effect of hydration on cognitive performance
Approval of ethic committee	Chinese Nutrition Society biomedical ethics committee
Ethical approval project identification code	CNS2015001
Date of approved by ethic committee	1 December 2015
Study type	Interventional study
Study design	Randomized parallel controlled trial
Key inclusion and exclusion criteria	Inclusion criteria: Aged between 18~25; Male; In health state, without metabolic disease, oral diseases, and so on. Exclusion criteria: Aged < 18, or age > 25; Female; With metabolic disease, oral diseases, and other diseases.
Interventions	Water supplementation
Outcomes	Urine osmotic pressure, Blood pressure, Mood, Thirsty, Cognitive performance
Collecting samples	Urine
Recruitment state	Finished
Randomization Procedure (please state who generates the random number sequence and by what method)	Primary sponsor generates random sequence with random number table.

**Table 2 ijerph-14-00966-t002:** The schedule of enrolment, interventions, and assessments.

	Enrolment	Allocation	Post-Allocation	Close-out
Timepoint	1 February 2016	14 March 2016	14 March 2016	30 March 2016
Enrolment:				
Eligibility screen	X			
Informed consent	X			
Allocation		X		
Interventions:				
Water supplementation			X	
Assessments:				
Baseline anthropometric measurements variables: blood pressure, height, weight, waist circumference	X		X	
Outcome variables: cognitive performances, mood, subjective sensation			X	X

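### No primary outcome is named: ten cognitive scores share a flat two-sided 0.05, and digit span, which sized the trial, has no priority in the analysis

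*Protocol article*

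**What the plan says.** Section 2.19 uses one mixed repeated-measures model to "investigate the effect of water supplementation on changes in urine index, mood and cognitive performances". It fixes one level for everything: "Significance levels will be set at 0.05", two-tailed, with 95% confidence intervals. It does not rank the outcomes.

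Section 2.3 sizes the trial on one variable: "The variable used for the calculation of sample size is digit span". It does not call that variable primary, and it does not say whether the forward, backward or total score is meant. Section 2.14 defines all three.

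The outcomes row of Table 1 reads "Urine osmotic pressure, Blood pressure, Mood, Thirsty, Cognitive performance", with none marked primary. The end of the Introduction orders the objectives by domain: cognition is to be evaluated first and mood explored second. No variable is named there either.

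**The concern.** The trial's first objective concerns cognition as a domain, but the domain is measured by ten scores and the plan does not say which one answers the question. A significant result on any of them could be reported as an effect of water on cognition, and the 5% error rate of each test does not carry over to that conclusion. The 80% power was bought for digit span, yet a null digit span result would count no more than a null result on any other score.

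This matters because the article describes earlier findings as conflicting and intends the results to support public education on drinking water. An isolated chance finding would add to the inconsistency that the trial is meant to resolve.

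**Working it through.** **Count of scores**

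- Cognition (section 2.14): digit span forward, backward and total (3); digit symbol (1); dose-work reading speed, error rate and IMC (3); creativity C-score (1); logic number correct and correct rate (2). Sum: 3 + 1 + 3 + 1 + 2 = 10.
- Mood (section 2.13): seven subscales plus TMD = 8.
- Together: 10 + 8 = 18.
- Urine indices are left out. Section 2.1 hypothesises that water improves hydration state, so no true null is expected for them, and they do not measure cognition or mood.

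**The plan's own figure, N = 68**

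The inputs are a difference of 1.0 ("with water supplementation and without water supplementation were 10.5 and 11.5, respectively"), "80% power is set", two-sided 0.05 and 10% drop-out. No SD is stated, so 68 cannot be reproduced, only back-solved. Per arm, n = 2 × SD² × (1.96 + 0.84)² / 1.0². With an assumed SD of 1.37 this is about 29.5, rounded to 30; 30 / 0.9 = 33.3, rounded to 34 per arm and 68 in total. An SD of 1.0 would give 36 in total and an SD of 2.0 would give 140. Depending on rounding and on a normal or t calculation, 68 corresponds to an SD of about 1.36 to 1.41.

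**Chance of at least one false positive if water does nothing**

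For k independent tests, the chance in either direction is 1 − 0.95^k, and in the benefit direction 1 − 0.975^k. For correlated scores, the k test statistics are taken as normal with equal pairwise correlation 0.5. That correlation is an assumption; the article gives none.

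| Scores | Either direction, independent | Either direction, correlation 0.5 | Favouring water, independent | Favouring water, correlation 0.5 |
|---|---|---|---|---|
| 1 (nominal) | 5% | – | 2.5% | – |
| 10 cognitive | 1 − 0.95^10 = 40% | 29% | 1 − 0.975^10 = 22% | 14% |
| 18 cognitive and mood | 1 − 0.95^18 = 60% | 40% | 1 − 0.975^18 = 37% | 20% |

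**Effect of the built-in overlap**

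Total score is forward plus backward, IMC is computed from letters read and errors, and TMD combines the mood subscales. The independent figures are therefore upper bounds. Simulating the 18 scores with approximations to these overlaps, and assumed correlations from 0 to 0.3 within cognition and 0 to 0.7 within mood, gives 43% to 56% in either direction and 23% to 33% favouring water. Even at a common correlation of 0.7 the 18 scores give 28% and 14%.

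**Why one primary rather than adjusting across all scores**

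With Bonferroni over 18 scores the level is 0.05 / 18 = 0.0028. At the back-solved SD of 1.405 and 31 evaluable per arm (34 × 0.9 = 30.6), power on digit span falls from 80% to about 42%. Restoring 80% needs 59 per arm, and 59 / 0.9 = 65.6, so 66 per arm and 132 in total. Naming one primary keeps 5% error and the planned 68.

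**The case against.** The strongest reply has four parts.

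- **Multiplicity rules often sit in an analysis plan that is not shown.** This stands as far as it goes: the absence of Holm or a similar procedure is not the charge. But which outcome decides the trial is a protocol-level choice. The article prints the significance level, the covariates, the scoring formulas and an outcomes row, so condensing a longer document does not explain the gap.
- **The domains are ranked.** This stands. The Introduction puts cognition first and words mood as exploratory, so the ten-score figures should lead and the 18-score figures are context. The ranking does not choose among the ten cognitive scores.
- **No success rule is stated.** Also true. That any one of ten scores would be enough is an inference from the flat level and the missing primary, not something the article says. Nothing in it prevents that reading.
- **The 40% and 60% exaggerate.** A reader might infer from them, or from a larger count that includes the urine indices, that a chance benefit of water is likely. The documents do not support this. Those figures count significant results in either direction, including harm, and assume independence that the score definitions contradict. The urine indices do not belong in the count. A spurious benefit is the less probable outcome in every scenario for the 18 cognitive and mood scores.

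**Conclusion.** The point holds. No primary outcome is named, ten cognitive scores are each tested at two-sided 0.05, and the one variable that sized the trial has no priority in the analysis.

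If water has no effect, the chance of at least one significant cognitive score is about 29% to 40%, roughly six to eight times the nominal 5% (29/5 = 5.8; 40/5 = 8). The chance of a spurious cognitive benefit is about 14% to 22%, roughly six to nine times the nominal 2.5% (14/2.5 = 5.6; 22/2.5 = 8.8). These ranges rest on an assumed pairwise correlation between 0 and 0.5; stronger correlation lowers them, but not to the nominal level. The count of scores and the flat 0.05 come straight from the article.

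This should be corrected, but it does not mean that a false claim of benefit is to be expected.

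**What to change.** Name as primary the one digit span score that underlies section 2.3. The sponsor must state which it is; the total score is a proposal, since the article does not say. Test it at two-sided 0.05 as the between-group effect from the repeated-measures model already stated, using test 1 and test 2, and base any claim of an effect on cognition on it alone.

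Report the other cognitive scores and the mood scores either as secondary, with Holm within each family, or as exploratory with 95% confidence intervals and no significance claims. Treat urine osmolality as a manipulation check.

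Record the date of the decision, and make it before the A/B group code described in section 2.7 is opened. Table 1 gives recruitment as finished and Table 2 gives close-out as 30 March 2016, so an undated choice would look post hoc.

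Before digit span carries the claim, reconcile the means in section 2.3. As printed they are 10.5 with water and 11.5 without, which runs against the hypothesised benefit if a higher score is better, as the scoring in section 2.14 implies.

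Cost: a dated statement and some redrafting, with N = 68 unchanged. The downside is that an isolated secondary score with p < 0.05 can no longer be presented as a confirmed effect.
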